### Success of Randomization

We will summarize baseline demographic, sexual behavior, and other characteristics assessed at the screening and enrollment visits for each trial arm to assess the success of randomization. Continuous data will be summarized as means and ranges and categorical variables as percentages. If appropriate, we will test differences between the study arms by standard t-tests for means and Fisher’s exact test for categorical variables.

### 12.7.3 Primary Objective and Secondary Objectives 1 & 3: Effectiveness

Cox proportional hazards models, stratified by study site, will be performed to compare the HIV incidence of the diaphragm arm with the incidence in the non-diaphragm control arm. We will consider the diaphragm and gel effective if the HIV infection rate among women randomized to the diaphragm and gel arm is statistically significantly lower than the infection rate among women randomized to the non-diaphragm arm with appropriate adjustment for multiple comparisons and correlated hypothesis tests. Our sample size and power will afford us to have 90% power to detect a relative hazard comparing incidence in women in the diaphragm arm compared to that in the controls of .67 corresponding to an intervention-related reduction of 33% as significantly less than one at the 5% level. Similar analyses will be performed with incident STI infections as secondary endpoints. In the per-protocol analyses, additional co-variates will be included in the hazards models, including frequency of diaphragm, gel, and condom use, and baseline characteristics that were statistically significantly different between the study arms at baseline. We also will conduct analyses, controlling for a number of STIs (*i.e.* TP, HSV-2, and TV), and evaluate these STIs as potential effect modifiers of a diaphragm-HIV relationship. All results will be reported as rate ratios with associated 95% confidence intervals.

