## Why Cover the Cervix?

There are several reasons why the cervix might benefit from the type of protection a diaphragm could offer. Cervical cells are fragile. Like the rectum, the cervix is lined with delicate columnar epithelial cells, infected far more easily than the tough squamous epithelium of the vagina. The cervix also stands guard to the upper genital tract, itself highly susceptible to infection. For these and other reasons, the cervix is the portal of entry for many bacterial (and possibly viral) STI pathogens known to increase susceptibility to HIV.2 Preventing such cervical infections could decrease the likelihood of HIV acquisition. But more compelling still, new evidence points to the cervix itself as the primary “hot spot” for HIV infection, independent of its role in acquisition of other pathogens.

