## 4.4 Secondary Objective 3 – Effect of Other Reproductive Tract Infections

Because sexually transmitted infections are co-factors for HIV transmission, it is likely that these conditions will modify any potential relationship between diaphragm use and HIV. To be able to control for this, we are testing for *Treponema pallidum*, herpes simplex virus type 2, and *Trichomonas vaginalis* and will evaluate them as potential effect modifiers of a diaphragm-HIV relationship. Additionally, some of these STIs preferentially infect cervical cells (*i.e.* HSV-2) while other conditions are susceptible to changes in pH such as the buffering action produced by Replens lubricant gel.11 Consequently, we have a unique opportunity to assess the protective effect of the diaphragm plus Replens lubricant gel on these secondary outcomes. We use urine PCRtests to detect *Trichomonas vaginalis*, Enzyme-linked immuno-sorbent assay (ELISA) to detect HSV-2, and rapid plasma reagin (RPR) and confirmatory treponemal tests (TPHA) to detect *Treponema pallidum*.

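### In the per-protocol hazards models, adjusting for diaphragm, gel and condom use leaves an arm rate ratio that is not an effectiveness estimate; the baseline covariate rule and the timing of STI adjustment also need fixing

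*Protocol*

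**What the plan says.** Section 12.7.3 sets out three layers of analysis.

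- **Primary:** "Cox proportional hazards models, stratified by study site, will be performed to compare the HIV incidence of the diaphragm arm with the incidence" among controls. The criterion for success is that "the HIV infection rate among women randomized to the diaphragm and gel arm is statistically significantly lower than the infection rate among women randomized", the comparator being the control group. No product-use, STI or other covariate is named.
- **Per-protocol:** here, and only here, "additional co-variates will be included in the hazards models, including frequency of diaphragm, gel, and condom use, and baseline characteristics". The characteristics meant are "baseline characteristics that were statistically significantly different between the study arms at baseline".
- **STI-controlled:** further analyses control for syphilis (TP), HSV-2 and trichomonas (TV), and also "evaluate these STIs as potential effect modifiers of a diaphragm-HIV relationship". No time point is given for STI status.

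Section 4.4 treats the effect on some of the same infections as a result in its own right: "we have a unique opportunity to assess the protective effect of the diaphragm plus Replens lubricant gel on these secondary outcomes". The Study Summary likewise lists TV and HSV-2 infection under the secondary objectives.

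Section 12.7 calls the intent-to-treat analysis the one that keeps randomisation intact. It warns that the per-protocol results may be confounded, and says that differences between the two will be discussed and weighed in interpreting the trial.

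**The concern.** Product use is recorded at quarterly follow-up visits (section 8.5), so it is a post-randomisation variable. Controls receive no study diaphragm until they leave the study (section 8.3). Diaphragm and gel use are therefore both the assigned intervention and close to a marker of arm. Once they are in the model beside arm, the arm term no longer carries the effect of the product.

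Condom use is different but also awkward. Women know their assignment, and section 12.7.4 plans to study how the diaphragm and gel affect condom use. Ordinary adjustment for a variable that responds to assignment does not in general give a valid direct effect.

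Two lesser points sit in the same paragraph. Choosing covariates because they differ significantly between randomised arms selects on chance, not on prognosis. And TV and HSV-2 appear both as outcomes and as variables to control for, without a time point.

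What is at stake is the reading of the supporting analyses. Section 12.7 gives them weight beside the primary result, and section 8.5 reports adherence below expectation, so they will be looked at closely. An arm rate ratio near or above 1 from such a model could be taken as no benefit, or harm, from a product that works.

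**Working it through.** **1. The plan's own figure.** Section 7.1.1 gives control incidence of 4%, 5% and 3.5% per year at sites contributing 49%, 29% and 22% of the sample, 2 years' accrual in a 3-year study, discontinuation of about 7% per year, 4,500 women and a hazard ratio of 0.67. With exponential hazards λ and dropout η (0.070 to 0.074), R = 2 and T = 3, the event probability is

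p(λ) = λ/(λ+η) × {1 − [e^(−(λ+η)(T−R)) − e^(−(λ+η)T)] / [(λ+η)R]}.

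Summing over sites and arms gives 279 to 281 events and about 4,000 woman-years per arm. For 280 events, power = Φ(|ln 0.67| × √280 / 2 − 1.96) = Φ(3.35 − 1.96) = 0.918. The stated 90% for the arm-only, site-stratified comparison is met, and nothing below changes it.

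**2. What the arm term means.** Let A be arm and D the fraction of acts with the product, with D = 0 in controls. If the effect acts only through use, the log hazard is α + βD. Fitting α + θA + βD then gives θ = 0, an arm hazard ratio of 1, whatever β is. If women at higher risk use less, low use marks high risk within the diaphragm arm, and θ absorbs this and rises above 0.

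**3. Size, by simulation (all inputs assumed).**

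- Simulation A: 400,000 women per arm, 4% per year, 1.4 years, mean use 72%, 45.5% protection at full use. Expected arm ratio 1 − 0.455 × 0.72 = 0.67.
- Simulation B: 300,000 per arm, control rate about 4% per year, 1.5 years, mean use about 0.7, log hazard ratio −0.58 at full use (or 0 for no effect). A risk factor U multiplies the hazard by e^(0.4U) and lowers the logit of use by cU.

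| Simulation | True effect | Use related to risk | Arm HR, arm only | Arm HR, arm + use | SE ratio |
|---|---|---|---|---|---|
| A | yes | no | 0.67 | 1.01 | 0.219/0.134 = 1.6 |
| A | yes | yes | 0.73 | 1.67 | – |
| B | yes | no (c = 0) | 0.69 | 1.02 | 2.8 |
| B | yes | c = 0.25 | 0.69 | 1.36 | 2.6 |
| B | yes | c = 0.5 | 0.69 | 1.63 | 2.4 |
| B | no | no (c = 0) | 1.00 | 0.95 | 2.8 |
| B | no | c = 0.25 | 1.00 | 1.39 | 2.6 |
| B | no | c = 0.5 | 1.01 | 1.76 | 2.3 |

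The 0.95 is compatible with 1.0 given simulation error. The standard error grows because arm and use are highly correlated (0.92 to 0.93 in B); the exact factor depends on the assumed spread of use. The use term is not safe either: in A with risk-related use, the full-use hazard ratio came out at 0.27 when the truth was 0.545.

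**4. Baseline selection.** With k independent tests at 5%, the chance that at least one covariate is selected by chance is 1 − 0.95^k: 40% for k = 10, 64% for k = 20, 79% for k = 30. The values of k and the independence are assumptions.

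**5. STI timing.** Status before randomisation exists for all three infections: TV at screening (section 9.3), TP and HSV-2 at enrolment (section 9.4). Follow-up status also exists (section 9.5). The illustration assumes a direct arm ratio of 0.8, an STI-to-HIV ratio of 2.1 (the HSV figure in Appendix 16.4), 50% infected at enrolment and a 30% base chance of new infection in controls.

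| Device effect on new STI | Unadjusted | Adjusted, baseline STI | Adjusted, follow-up STI |
|---|---|---|---|
| none | 0.791 | 0.791 | 0.791 |
| risk ratio 0.67 | 0.766 | 0.766 | 0.795 |
| risk ratio 0.5 | 0.760 | 0.760 | 0.803 |

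Baseline adjustment leaves the arm effect alone. Follow-up adjustment moves it modestly toward 1, and only if the device prevents the STI.

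**The case against.** The strongest reply is that this concerns supporting analyses the protocol already labels as less stringent and open to confounding. That stands, and it limits the weight of the point. It does not remove it: the caveat is about confounding, whereas the arm coefficient changes meaning even with no confounding at all.

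A second reply is that section 8.5 wants effects among perfect users, never users and those between, so the use term rather than the arm term may be the target. That is plausible. But section 12.7.3 adds the use variables to the arm model, promises rate ratios for all results, and does not say which term will be read. The use term is itself open to strong confounding, as simulation A shows.

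A third reply is that the composition of the per-protocol set and finer detail are left to a data analysis plan. True of the set; but the covariates and the significance rule are fixed in the protocol text.

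Several stronger readings are tempting and not supported:

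- *That the trial's effectiveness result is distorted.* The primary model and success rule contain none of these covariates.
- *That the protocol adjusts for follow-up STIs.* No timing is stated, and baseline adjustment would be legitimate.
- *That STI adjustment removes the benefit hypothesised in section 3.1,* "Preventing such cervical infections could decrease the likelihood of HIV acquisition". Chlamydia and gonorrhoea, the main bacterial cervical infections in the protocol's rationale, are not among the STIs listed as examples for adjustment. HSV-2 does fit that rationale, but the simulated shift is small.
- *That significance-based selection biases the arm effect.* These are true baseline variables; the cost is efficiency and a data-driven model.
- *That falling condom use shows bias from adjusting for it.* If coverage fell from 70% to 50% in the diaphragm arm with 80% condom efficacy (all assumed), a ratio of 0.67 would appear as 0.67 × (1 − 0.8 × 0.5)/(1 − 0.8 × 0.7) = 0.67 × 0.60/0.44 = 0.91. That is dilution of the intent-to-treat contrast. If anything, it is a reason to want a sound condom-adjusted analysis.

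**Conclusion.** The point holds for the per-protocol hazards models only. With diaphragm and gel use in the model, the arm rate ratio does not estimate effectiveness, and this follows from the design without any simulation. The size does rest on assumptions about mean use, its spread and its link with risk. Under those tried, a true benefit near one third reads as about no effect, or as an apparent 1.4 to 1.7-fold excess, and a product with no effect can read as 1.4 to 1.8. For condom use the objection is one of principle: it may respond to assignment, and no size is claimed.

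The baseline rule is a poor choice with little bias. The STI timing is an ambiguity to close, not a demonstrated error; its consequence, if follow-up status were used, is a shift of roughly 0.77 to 0.80 under assumed inputs. The planned power and the primary conclusion are untouched. The change is worth making because these analyses will inform interpretation and the correction is cheap.

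**What to change.** - **Product and condom use.** State that no arm effect adjusted for diaphragm, gel or condom use will be reported. Estimate the adherence effect separately, for example with a randomisation-based complier effect. State its assumptions: assignment acts on HIV only through product use, which is doubtful if condom use shifts on its own, and self-reported use is adequate. State also that it is less precise.
- **Condom-adjusted results.** Label any such analysis exploratory. A marginal structural model is one option, not a required change.
- **Baseline covariates.** Replace the significance rule with a short prespecified list of prognostic screening or enrolment variables, such as age, STI status and condom use at entry.
- **STIs.** Restrict adjustment and effect modification by TP, HSV-2 and TV to screening or enrolment status, and treat follow-up infections as outcomes.

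The cost is a revised paragraph in section 12.7.3 and modest programming. All the data needed are already collected. The adherence estimate will have a wider interval than the intent-to-treat one.

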### 12.7.4 Secondary Objectives 2 and 4: Acceptability and Feasibility

More details on the analyses will be provided in the separate protocol to be developed. Briefly, we will measure women’s experiences with the diaphragm and gel in structured interviews at follow-up visits and in focus group discussions and/or in-depth interviews using the following groups of variables: 1) general acceptability of the diaphragm and gel (assessments of best and worst features. willingness to recommend to a friend), problems with use and re-use, and factors related to diaphragm hygiene, 2) effects of diaphragm and gel use on sexual activity (*e.g.* changes in sexual pleasure and in coital frequency), ability to hide use from partner when so desired; and 3) general acceptability, and effects of diaphragm and gel on condom use. We will calculate overall rates of key acceptability and feasibility variables, as well as an overall acceptability rating, at the start and end of the trial (visits at month 3 and month 24 or closing visit, if it is before 24 months). We will also calculate factors noted by study staff and ascertained from study and clinic records such as the need for re-fitting and requests for new products. We will also evaluate changes in acceptability over time by comparing key acceptability variables by study arm and by visit, the overall acceptability rating by study arm and by visit, and each woman’s first acceptability report with her last one. We will use generalized estimating equations to perform the first two analyses and McNemar’s Chi-square tests to perform the last. Logistic regression models will be used to evaluate effects of demographic and sexual co-variates on the overall acceptability rating at various time points.

# 13 Human Subjects

## 13.1 IRB Review

The protocol requires that written informed consent must be obtained from all study participants. The protocol has been approved by IRBs of UCSF, Ibis Reproductive Health, MRC, the University of Zimbabwe, and PHRU. The protocol has been shared with the Ministries of Health in South Africa and Zimbabwe and additional local, regional or national ethics approval boards as necessary or required.

## 13.2 Confidentiality

All interviews and clinical exams are conducted in private and all study-related information is stored securely at the study site, in locked file cabinets. All records and specimens are identified by ID numbers only to maintain participant confidentiality. Completed study forms are kept in locked files at the study sites. All records that contain names or other personal identifiers, such as the study register, locator forms, signed informed consent forms, logbooks, cash books and appointment book are kept locked separately from records identified by ID number. All local databases are password-protected. Data that are transmitted electronically do not contain any identifying information. While regulatory agencies, study monitors, and auditors or their designees may have access to study records, the identity of participants remains confidential.

Although study staff make every effort to protect privacy and confidentiality, a participant’s involvement in the study could become known to others and social harms may result if study participation is associated with being at high risk for HIV infection. To minimize such stigma, much emphasis is placed on community outreach to educate the community about HIV/AIDS, diaphragms, and this clinical trial.

## Compensation

Participants receive a monetary reimbursement at each scheduled study visit for transportation to and from the clinic for the clinic-based cohort study, time spent in the study and any other costs which are associated with the volunteer's participation in the study. Participants who return for unscheduled visits or visits that are scheduled for medical follow-up or treatment are reimbursed for transport costs at the discretion of the site coordinators on a case-by-case basis. Site-specific reimbursement amounts are determined by each site and are comparable to amounts given to participants in other studies in the surrounding areas. The determined amount for a site is stated in its Informed Consent Form. All reimbursement amounts are approved by the sites’ local IRBs. Sites may choose to provide reimbursement in the form of food/grocery coupons if they cannot safely keep cash on hand.

## Benefits and Risks

Participation in this trial involves numerous benefits, including diagnosis and treatment of STIs, pregnancy testing, HIV counseling and testing, safer-sex counseling, and free male condoms. Women who test positive for HIV at screening are offered psychosocial support by study staff and psychosocial and medical referral as needed. Women who seroconvert for HIV during the trial receive psychosocial and medical services as needed from study staff or referral to such services in the community as appropriate and feasible at each study site. For example, in Zimbabwe, we have established weekly support groups for HIV-infected women identified in all of our studies. Male partners of participants are eligible for free STIs diagnosis and treatment as well as referral for HIV counseling and testing or provision of free testing at the site. Participants and others may benefit in the future from the trial results. Specifically, the trial results may lead to knowledge about whether the latex diaphragm with Replens gel can help to protect women from HIV infection.

Study risks are minimal because diaphragms and Replens gel have been deemed safe by regulatory agencies and have been used widely for decades. However, a small percentage of women may discover that they are allergic to latex and may experience adverse effects before being discontinued from the study. In addition, there may be an increased risk of developing urinary tract infections and Toxic Shock Syndrome with diaphragm use. Furthermore, participants may experience minimal vaginal bleeding and/or discomfort during or after the enrollment pelvic exam. Finally, participants may become embarrassed or anxious when receiving HIV counseling or test results. Being diagnosed with HIV or another STI may cause stress on relationships. Trained counselors are available to help participants with these feelings.

## Trial Closure Considerations

UCSF reserves the right to terminate the trial prematurely at one or more sites if study participant recruitment is too slow, if study participant retention in the study is insufficient, if undue risk related to the study intervention arises, or if there are serious deviations from the study protocol.

# 14 Administrative Procedures

## Investigator Responsibilities

The co-PIs obligate themselves and all study staff to:

- Conduct the study in accordance with the relevant, current protocol, and not make changes without permission of the sponsor (UCSF) except when necessary to protect the safety, rights or welfare of participants.
- Personally conduct or supervise the described investigations.
- Inform participants in the study that use of the study products for the prevention of STIs is under investigation and ensure that requirements relating to obtaining informed consent and IRB review and approval are met.
- Report AEs and SAEs that occur in the course of the investigation to UCSF in accordance with this protocol.
- Understand the designated use of the Ortho All-Flex diaphragm and Replens gel, including the potential risks and side effects
- Ensure that all associates, colleagues, and employees assisting in the conduct of the study are informed about their obligations in meeting the above commitments.
- Maintain adequate and accurate records in accordance with this protocol and make those records available for inspection to study monitors and auditors or their designees, and store them at the study site.
- Ensure that an IRB that complies with the requirements of 45 CFR 46 will be responsible for the initial and continuing review and approval of the clinical investigation.
- To promptly report to the IRB all changes in the research activity and all unanticipated problems involving risks to human subjects or others.
- To not make any changes in the research without IRB approval except where necessary to eliminate apparent immediate hazards to human subjects.
- Comply with all other requirements regarding the obligations of clinical investigators and all other pertinent requirements in 45 CFR 46.

As part of the above responsibilities, the study site co-PIs are obliged to maintain a regulatory binder on-site, containing at a minimum the following documents:

- Contractual agreements between UCSF and their site (sub-award documents in the case of the South African sites and Memorandum of Agreement between UCSF and the University of Zimbabwe).
- The original signed study protocol and all amendments, clarifications, addenda, documentation of protocol deviations, *etc*. The co-PIs must sign and date the cover page of this study protocol and all subsequent amendments.
- Ortho All-Flex manufacturer insert and instructions.
- Replens manufacturer insert and instructions.
- Locally approved consent forms (English and local language versions), records of IRB approval, records of IRB annual review, and all other IRB correspondence.
- Local approval for importation of study device and accountability records.
- Listing of local laboratories, documentation of their accreditation to perform protocol-specified testing for which they have been contracted, CVs of laboratory staff involved in the testing for this study, and laboratory test normal values.
- Study staff roster, signature log and CVs for all staff members.
- Study monitoring visit log.
- Monitoring and progress reports.

All study sites will weekly progress reports using a format designed jointly by UCSF and Ibis Reproductive Health to the co-PIs, and other key trial management personnel describing the number of participants screened, enrolled and completed, reasons for study discontinuation, numbers of AEs reported, a description of all SAEs, and unanticipated problems.

